To examine the impact of the intervention, in the first 1-2 weeks following training, cohorts of children 5-15 years old will be recruited and screened using the parent report version of the Strengths and Difficulties Questionnaire (SDQ) that corresponds to the age of their child. The SDQ has been validated in Iran and yields measures of symptoms, functioning, and family burden plus overall scores and domain scores for hyperactivity and emotional, peer relationship, and conduct problems. In studies in other countries, the SDQ has been found to have similar or better sensitivity and specificity as the much longer CBCL (Goodman 1999). Screening results will not be shared with the GP, and summary scores will not be discussed with parents. Parents and children/youth will be free to discuss the screen with the GP or anyone else, and RAs administering the screens will encourage parents to discuss any concerns they have with their GP. Those children/youth who screen positive will be followed by telephone with re-assessment at 3 and 6 months after screening (regardless of whether or not the GP has considered them to have a mental health problem and entered them in the TUCCP registry).

The following figure is the currently planned timeline for the study, assuming recruiting of GPs in February-March, 2018 and beginning the trial in March-April, 2018.

| Study year          | 2016 7       | 2017 8       | 2018 9       | 2019  |
|---------------------|--------------|--------------|--------------|-------|
| month               | JASONDJFMAMJ | JASONDJFMAMJ | JASONDJFMAMJ | JASO  |
| Formative work      | XXXXXXXXXX   |              |              |       |
| Pilot training      |              | X XX         |              |       |
| Recruit GPs         |              | X            |              |       |
| GP group 1          |              | TRFF         | FFFFW        |       |
| GP group 1          |              | CRFF         | FFFF         |       |
| GP group 2          |              | TR           | FFFFFW       |       |
| GP group 2          |              | CR           | FFFFF        |       |
| GP group 3          |              |              | TRFFFFFW     |       |
| BP group 3          |              |              | CRFFFFFF     |       |
| Crossover trainings |              |              |              | T T T |

GP=general practitioners  

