In cluster-randomized studies, sample size is dependent on the extent to which outcomes are correlated within clusters. A review of adult primary care studies from high-income countries found ICC's for depression outcomes ranging from .016 to .035; the range for the SF-36 mental health measure was .009 to .033 with an overall median of 0.01 (Adams 2004). Given that we plan to enroll 45 general practitioners we would have clusters of 6 patients per general practitioner yielding a design effect of  $1+(6-1)*.01=1.05$ , or a sample size at outcome of about

284. Assuming a worst-case of 20% loss of patients to follow-up would require enrolling 355 patients.

There are varying estimates of the prevalence of high/abnormal SDQ scores ( $\geq 17$ ). We found 24% of those screened to be in this range in a study of children 6-16 in primary care in the US (Wissow 2008); Alavi and colleagues (2010) found a prevalence of 26% using this scoring of the SDQ in a population-based sample of children 6-11 in Tehran. Using an estimate of 24%, we then need to screen about 1479 children/youth.

For screening, we will recruit consecutive patients as they come for clinic visits. Families will be approached by a research assistant when they arrive for visits and asked if they are interested. Families will not be approached if the child appears to be acutely ill or in pain. If the family is interested, they will be taken to a nearby private space to discuss and consider consent/assent. We anticipate that most families will complete baseline data collection by telephone to avoid delaying their visit and to assure privacy. If time and privacy permit, consenting families will have the option to complete data collection in person before or at the end of the visit. To facilitate telephone administration, families will receive blank copies of the main questionnaires to use, if they desire, as references when later answering over the phone. Families who consent will receive a small token (value about \$2).

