### **Data collection**

Baseline data collection will take place at the time of enrollment or by telephone after the GP visit. Cognitive interviews and pilot testing will help assure that respondent burden is acceptable and achievable in a reasonably brief telephone call; should the plan proposed in this application require changes we will submit amendments to the protocol. The investigators have experience using the SDQ by telephone in Iran, and the GHQ (see below) by telephone in the US. The

research assistant administering the instruments will enter the responses into a secure electronic data base that will a) determine if the family is to be entered into the follow-up phase of the study (ie, child “positive” at the “possible” or “probable” level on the SDQ) or if responses to the parent self-harm question on the GHQ triggers notification of the GP. There will also be a brief exit survey for the parent and for older children/youth after the index visit. This will be administered by the research assistant in person at the GP office; however, as above, if lack of privacy or time do not permit, the survey can be administered by telephone.

The GHQ (General Health Questionnaire) is a brief instrument (28 items) used to rate adult emotional status. Parent mood is an independent predictor of treatment adherence and outcomes for children’s mental health services, and a separate target of TUCCP care. The GHQ can be used categorically with good sensitivity and specificity for psychiatric disorder, and as a continuous measure of distress. Its questions are framed in terms of recent changes in mood, which make it suitable for use in longitudinal studies, and it has been used in several studies in Iran (Emmami 2007).

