As noted above, we will not share screening results with the GPs, though we will tell parents that they are free to talk with their GP about the screening and their answers. We have made this decision based on the pragmatic nature of this trial. Initiation of universal or even consistent indicated screening is technically challenging and, were we to be initiating it as part of the study, would not likely be continued. That would be a threat to the generalizability of our results. Future studies may be able to address the costs and benefits of routine screening being part of the support offered by participation in TUCCP.

Child/parent follow-up data collection. An abbreviated data set (the key mental health outcome measures – SDQ and GHQ) will be collected by telephone three months after the initial visit for both the control and intervention children/parents; a longer final data collection will occur at six months after the initial visit. We will only follow those families whose child screened positive on the SDQ at the index visit, or for whom the SDQ was negative but the GP entered the child in the TUCCP database. It will not be possible to guarantee that research assistants making follow-up calls will be blind to the child's control-intervention status because assistants who recruit families will, when possible, also make follow-up calls so that a known person is maintaining contact. However, the assistants will have no other information about the family other than what is reported on the study instruments. In particular, they will have no knowledge of any data about the child from the TUCCP database, and they will administer the SDQ and GHQ prior to instruments (at the baseline and final visit) that might reveal information about use of any mental health services. We believe that the families' familiarity with the research assistant, coming from an in-person contact at the time of consenting, will promote follow-up. We believe that this advantage balances out concern about biased outcome assessment.

The literacy rate varies among the families to be recruited, and we anticipate that some parents will require that the consent forms (and instruments if done in person) will be read to them. This will take place in private, and we will have a sufficient number of female research assistants so that there are no barriers to participation because of staff gender.

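### Most baseline SDQs are expected by telephone after the visit with an already-trained GP, so the arm can affect who enters and the baseline score; other passages imply an earlier SDQ

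*Protocol*

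**What the plan says.** Study procedures puts screening after GP training: "in the first 1-2 weeks following training, cohorts of children 5-15 years old will be recruited and screened". Under Population and recruiting, families are approached on arrival and consent in a private space. For the questionnaires, "We anticipate that most families will complete baseline data collection by telephone to avoid delaying their visit and to assure privacy". They are given blank forms to use "as references when later answering over the phone". If time and privacy allow, "consenting families will have the option to complete data collection in person before or at the end of the visit". Data collection fixes when the call happens: "Baseline data collection will take place at the time of enrollment or by telephone after the GP visit".

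The score has three uses.
- Data collection has the database "determine if the family is to be entered into the follow-up phase of the study" from the SDQ result, and Data management says the data center scores the baseline SDQ to establish eligibility.
- Data analysis approach lists initial SDQ scores among the patient-level covariates.
- The sample size in Population and recruiting rests on outcome minus baseline.

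The parent exit survey asks whether a mental health problem was discussed and what follow-up was planned. Of this survey, Data collection says: "This will be administered by the research assistant in person at the GP office". The same sentence then allows it by telephone where time or privacy is lacking. On order, the paragraph on child and parent follow-up (Treatment and control interventions) says of the research assistants: "they will administer the SDQ and GHQ prior to instruments (at the baseline and final visit) that might reveal information".

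**The concern.** The two arms are trained to hold different visits. Intervention training covers engaging families, parent-child interaction and first-line treatment. Control training covers recognition and talking with families about options at the community mental health center. A parent who has just had one of these visits may rate the child as having more problems than before, or fewer, and the change need not be the same in both arms.

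If the SDQ is taken after that visit, both the set of children called SDQ+ and their baseline values are measured after the randomised exposure has begun. Selecting on such a score, adjusting for it or subtracting it can each produce a difference between arms that is not a treatment effect. Intent-to-treat by GP assignment keeps the labels right but does not restore comparability among the children selected.

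The order in which instruments are given is also at stake. The protocol accepts unblinded follow-up callers partly because the SDQ and GHQ come before anything that reveals service use. An exit survey done at the office, followed by an SDQ on the telephone, would reverse that order at baseline.

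**Working it through.** **1. The passages on timing, side by side.**

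| Place in the protocol | Timing implied for the baseline SDQ |
|---|---|
| Population and recruiting | telephone, later, for most families; in person before or at the end of the visit for the rest |
| Data collection | at enrollment, or by telephone after the visit |
| Follow-up paragraph (Treatment and control interventions) | children screened positive at the index visit |
| Summary of clinical data collection table | index visit at recruiting, in a row before the post-visit row |
| Oversight, items 6 and 8 | completing the instruments may prompt questions and concerns that families raise with the GP |

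The first two rows put most SDQs after the visit. The last three read as if the SDQ comes at or before it. No passage requires it before GP contact, sets a window for the call, or plans an analysis by timing.

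**2. The plan's own figure.** Inputs from Population and recruiting: difference 2.5, SD 7.2, correlations 0.37 (baseline with outcome) and 0.55 (between outcomes), alpha 0.05 (two-sided assumed), power 0.80. With one baseline and two outcomes the variance factor is (1 + 0.55)/2 + 1 − 2×0.37 = 1.035. Then n = 2 × 7.2² × 1.035 × (1.960 + 0.842)² / 2.5² = 134.8, so 135 per arm. Next, 270 × 1.05 = 283.5 (284); 284/0.8 = 355; 355/0.24 = 1479. All match the protocol. The arithmetic is sound, and it confirms that the baseline SDQ is a term in the powered contrast.

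**3. Upper illustration.** Assumptions, not in the documents: normal scores, every child in one arm shifted by d, none in the other, all baselines post-visit, no carry-over into later reports, no true effect. Cut-off 17, 24% positive, SD 7.2 and r = 0.37 are the protocol's figures.

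- Unshifted mean: m = 17 − 7.2 × 0.706 = 11.91.
- Share positive: P = 1 − Φ(a), with a = (17 − m − d)/7.2. For d = 0, P = 0.240. For d = +1, a = 0.567 and P = 0.285.
- Mean baseline among positives: m + d + 7.2λ, with λ = φ(a)/P. Unshifted: 11.91 + 7.2 × 1.295 = 21.24. Shifted: 12.91 + 7.2 × 1.191 = 21.49.
- Mean outcome among positives: m + 0.37 × 7.2λ. Unshifted 15.37; shifted 15.09.
- Change score: 15.37 − 21.24 = −5.88 (before rounding) against 15.09 − 21.49 = −6.40. The false difference is −0.53.
- Baseline-adjusted: at the same recorded baseline the shifted arm's expected outcome is lower by 0.37 × d, so −0.37.

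For d = +2 the figures are 33.4%, −0.74 and −1.06. Simulation agrees to within 0.02 points and 0.1 percentage point; for d = +1 one run gave 28.6%, 0.36 and 0.52. A positive shift in the intervention arm flatters the intervention; a negative one counts against it.

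**4. Weaker assumptions.**
- *75% of baselines post-visit (assumed), d = +1.* Share positive is 0.75 × 0.285 + 0.25 × 0.240 = 0.274. Bias is about 0.29 adjusted and 0.41 on change.
- *75% post-visit, d = −1.* Share positive is 20.9%. Bias is about 0.27 and 0.37 in the other direction.
- *Equal shift in both arms.* No bias.
- *Shift only where the GP discussed a problem.* Assume 75% post-visit; discussion in 40% against 20% of children with true scores of 15 or more and in 10% against 5% of the others; and a 2-point shift where discussed. Share positive is 26.8% against 25.4%. Bias is about 0.13 adjusted and 0.19 on change, which is 5% and 8% of 2.5.

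**The case against.** Telephone collection was chosen for stated reasons: not delaying the visit, and privacy. That most families will use it is an expectation, not a rule, and completion before the visit is allowed. Control GPs also receive training in recognition and in talking with families, so part of any visit effect may be common to both arms and cancel. The trial also describes its aim as preliminary evidence. All of this stands, and it limits how large the problem is likely to be. It does not remove the problem, because nothing in the protocol gives grounds to expect equal shifts in the two arms.

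A reader might infer that the protocol breaks its own rule on instrument order. The documents do not support that. The exit survey is in person by default but may be moved to the telephone for lack of time or privacy, and those are the reasons given for telephone baselines. Where both instruments are done by telephone, the SDQ can still come first. That rule also serves to keep the assistant unaware of service use; it was not written to protect the parent's answers from the visit. The order is at risk, not necessarily broken.

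A reader might also take the half-point change-score figure as the expected bias. It is not: it shifts every child in one arm only and assumes that no SDQ is taken before the visit.

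**Conclusion.** The concern holds as a problem of timing and of inconsistent text. Most baseline SDQs are expected after a visit that is already part of the randomised exposure, while other passages assume the SDQ comes at or before that visit. Because the score gates entry, enters the model and is subtracted in the powered contrast, the arm can affect selection and baseline alike.

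The documents give neither the size nor the sign of the bias. Under the assumptions shown, a 1-point shift confined to one arm gives at most about 0.37 (adjusted) to 0.53 (change) points, or 15% to 21% of the 2.5-point target. The scenario with a shift only after discussion gives 5% to 8%, and an equal shift in both arms gives nothing. The SDQ is also not the only way in: SDQ-negative children whom the GP registers are followed too, and that route likewise depends on what the GP does after randomisation.

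This should be fixed. It does not by itself invalidate the trial, but the timing of a baseline cannot be corrected after the data are collected.

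**What to change.** Reconcile the passages in step 1 so that they state one rule for when the baseline SDQ is taken. Then:

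1. Make the SDQ before GP contact the default where time and privacy permit, in the private space already used for consent. Leave the GHQ, EQ-5D-5L, demographics and service use for the telephone.
2. Where that is not possible, always give the SDQ before the exit survey.
3. Record for each child whether the SDQ was taken before or after the visit.
4. Compare by arm the SDQ+ share among those screened and the baseline SDQ.
5. Pre-specify a sensitivity analysis restricted to children with a pre-visit SDQ.

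The cost is some delay before the visit for a 33-item form, longer where it must be read aloud. Answering it first may prompt discussion with the GP in both arms, which sits uneasily with the decision not to make screening part of care. The pre-visit subset will be smaller and possibly selected, so item 5 supports the main analysis and does not replace it. Items 2 to 5 cost little and are worth having even if item 1 proves feasible for only some families.

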### **Data collection**

Baseline data collection will take place at the time of enrollment or by telephone after the GP visit. Cognitive interviews and pilot testing will help assure that respondent burden is acceptable and achievable in a reasonably brief telephone call; should the plan proposed in this application require changes we will submit amendments to the protocol. The investigators have experience using the SDQ by telephone in Iran, and the GHQ (see below) by telephone in the US. The

research assistant administering the instruments will enter the responses into a secure electronic data base that will a) determine if the family is to be entered into the follow-up phase of the study (ie, child “positive” at the “possible” or “probable” level on the SDQ) or if responses to the parent self-harm question on the GHQ triggers notification of the GP. There will also be a brief exit survey for the parent and for older children/youth after the index visit. This will be administered by the research assistant in person at the GP office; however, as above, if lack of privacy or time do not permit, the survey can be administered by telephone.

The GHQ (General Health Questionnaire) is a brief instrument (28 items) used to rate adult emotional status. Parent mood is an independent predictor of treatment adherence and outcomes for children’s mental health services, and a separate target of TUCCP care. The GHQ can be used categorically with good sensitivity and specificity for psychiatric disorder, and as a continuous measure of distress. Its questions are framed in terms of recent changes in mood, which make it suitable for use in longitudinal studies, and it has been used in several studies in Iran (Emmami 2007).

Parents will be asked to completed the EuroQol EQ-5D-5L, a brief (6 item) instrument that measures five areas of function (mobility, self-care, usual activities, pain/discomfort, anxiety/depression) at five levels. It will offer us the opportunity to understand the impact of parental disability which may or may not include mental health concerns disclosed on the GHQ. The EQ-5D-5L can be administered by telephone and is sensitive to a wide range of chronic conditions including mood and chronic pain problems in general populations (Agborsangaya 2014). Unlike many instruments, the EQ-5D-5L is scored by comparing the pattern of responses across the five areas to a population-based data ranking the relative value respondents place on each pattern of disability. A Farsi version of the EQ-5D-5L has been developed and a value set for Iran has been developed to guide its interpretation (Kiadaliri 2015).

Parent satisfaction with care will be assessed by asking parents if the visit involved discussion of a mental health problem, and, if so, if the GP suggested a plan for treatment (Brown 2008). Subsequently we will ask about satisfaction using questions initially developed by Zastowny and colleagues (1983) based on Hulka’s (1970) conceptualization of satisfaction with providers’ interpersonal skills and technical competency. Two questions ask about overall satisfaction with the visit, three reflect satisfaction with informativeness (was the doctor’s information helpful, did the doctor clearly explain what you should do, answer all your questions) and four reflect partnership (did the doctor encourage you to talk about your worries, ask for your opinion about treatment, spend enough time with you, treat you with respect). In past work (Wissow 1998) we found that while the overall satisfaction and informativeness items are skewed to higher ratings (a ceiling effect), the partnership items are sensitive to differences in provider interaction style, which is targeted by one of the components of the intervention training.

Table: Instruments completed by patients/family

| Instrument name                                     | Respondent                  | Timing/method of administration*          |
|-----------------------------------------------------|-----------------------------|-------------------------------------------|
| Strengths and Difficulties Questionnaire (33 items) | Parent about child          | Baseline and 3 and 6 months later if SDQ+ |
| General Health Questionnaire (28 items)             | Parent about self           | Baseline and 3 and 6 months later if SDQ+ |
| Patient and family demographics (22 items)          | Parent about self and child | Baseline                                  |
| Health status EQ-5D-5L (6                           | Parent about self           | Baseline and 6 months later if            |

|                                                                                     |                             |                                     |
|-------------------------------------------------------------------------------------|-----------------------------|-------------------------------------|
| items)                                                                              |                             | SDQ+                                |
| Satisfaction with GP interpersonal and technical skills [exit interview] (15 items) | Parent about self           | Baseline                            |
| Use of community services (6 items)                                                 | Parent about self and child | Baseline and 6 months later if SDQ+ |

\* note that all completed by telephone except some baseline instruments may be completed in-person at the time of the index GP visit

